#### Other outcome measures

The Modified Ashworth Scale (MAS) grades muscle tone or spasticity on a scale of 0 to 4, with 0 representing no increase in muscle tone and 4 indicating that the muscle causes joint rigidity either in flexion or in extension. The MAS is the primary clinical measure of spasticity following stroke; however, a variety of authors have reported inconsistent inter-rater reliability and validity of the tool with ranges between poor and excellent. The MAS is assessed for the biceps brachii, triceps brachii, anterior deltoid, and flexor digitorum muscles of the fingers before and after each tDCS session [23]. This assessment has been utilized in numerous research studies as a measure of spasticity in patients with upper motor neuron lesions [23].

### Participant timeline {13}

Table 1 displays the timing of the tDCS intervention arms, as well as the timing of each outcome measure. The post-allocation period is repeated at each visit with a different tDCS intervention (anodal, cathodal, sham, or bilateral), for a total of four visits.

**Table 1 Tab1:** Schedule of enrollment, interventions, and assessments

	**Study period**							
	**Enrolment**	**Allocation**	**Post-allocation**					**Close-out**
**Timepoint**	*** − t***_***1***_	**0**	***t***_***1***_	***t***_***2***_	***t***_***3***_	***t***_***4***_	***t***_***5***_	***t***_***x***_
**Enrollment:**								
**Vitals**	X							
**Informed consent**	X							
**Allocation**		X						
**INTERVENTIONS:**								
***TMS (anodal, cathodal, sham, or bilateral)***				X				
***Washout***							X	
**Assessments:**								
***TMS***			X		X			
***FM-UE***	X		X		X			
***MAS***			X		X			
***Monitor 10–15 min for adverse effects***						X		

### Sample size {14}

Study personnel aim to enroll up to 30 participants (15 female) in the event of a potential attrition rate of 15%. Based on our preliminary data [24], we estimated that the targeted effect size for our study is 0.42 (SD: 0.13). The power analysis was performed by using GLMMPSE Sample Size Software (https://samplesizeshop.org/) [25]. Based on our preliminary data from a pilot trial (ClinicalTrials.gov Identifier: NCT05174949) [24] and the proposed basic statistical analysis on the primary and secondary outcomes (see the “Statistical methods” section), we determined the sample size of 26 will give 80% power at the 5% significance level for the targeted effect size. We will include a total of 30 stroke participants (15 female) for this clinical trial study to account for an attrition rate of 15% based on our previous experience in similar multiple-visit brain stimulation research.

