## Objectives {7}

This study aims to determine how targeted high-definition transcranial direct current stimulation (THD-tDCS) changes the excitability of the contralesional cortico-reticulospinal tract (CRST) and ipsilesional cortico-spinal tract (CST), thus reducing the expression of the flexion synergy and spasticity.

Specifically, the study aims are as follows:Aim one of this study is to evaluate the degree of change of excitability of the CST following anodal Targeted High-Definition transcranial direct current stimulation (THD-tDCS) over the ipsilateral primary motor cortex (iM1) (Fig. 1c). Specifically, we aim to determine whether this stimulation simultaneously reduces contralesional CRST hyperexcitability, while enhancing motor function in the involved upper extremity in participants in the post-acute phase of stroke recovery.Aim two is to evaluate the degree of reduction in CRST hyperexcitability as evidenced by a reduction in spasticity and flexion synergy in the involved upper extremity, following cathodal THD-tDCs over the contralesional dorsal premotor cortex (cPMd) in participants in the post-acute phase of stroke recovery (Fig. 1d).Aim three combines the first two aims—to evaluate the confluent effect of bilateral THD-tDCS, when given simultaneously using anodal stimulation over iM1 and cathodal stimulation over cPMd (Fig. 1e), on the excitability of CST and CRST, as evidenced by a decrease in the expression of flexion synergy and spasticity, as well as an improvement in UE function.

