## Statistical methods

### Statistical methods for primary and secondary outcomes {20a}

All outcome measures are continuous and correlated in a pretest/posttest format, requiring analysis with longitudinal linear modeling for correlated data analysis. We utilize generalized estimating equations (GEE) in SAS 9.4. GEE analysis is beneficial as it offers an unbiased estimation of population-averaged regression coefficients despite possible misspecification of the correlation structure even when the data is not normally distributed. Intervention type (anodal, cathodal, bilateral, and sham) and the time point (before or after stimulation) are defined as fixed factors. The study participants are defined as random factors. Carry-over effects will be examined using an extension of Grizzle’s classic crossover design [28]. All analyses are conducted using SAS 9.4 (Carey, NC) with an alpha = 0.05.

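### Enrolling 30 falls just short of covering 15% attrition around a required 26, and the 26 cannot be reproduced from the effect size as printed

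*Protocol article*

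**What the plan says.** Everything at issue is in the protocol article, mostly under Sample size {14}.

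- The effect: "the targeted effect size for our study is 0.42 (SD: 0.13"). It is attributed to pilot data. The text does not say whether 0.42 is standardised or raw, which outcome or contrast it belongs to, or what the 0.13 is the SD of.
- The tool: "The power analysis was performed by using GLMMPSE Sample Size Software". The calculation is tied to the primary and secondary outcomes together.
- The result: "we determined the sample size of 26 will give 80% power at the 5% significance level for the targeted effect size".
- The allowance for losses: "We will include a total of 30 stroke participants (15 female) for this clinical trial study to account for an attrition rate of 15" per cent.

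Two other sections bear on it. Statistical methods {20a} describes the model: "Intervention type (anodal, cathodal, bilateral, and sham) and the time point (before or after stimulation) are defined as fixed factors". It sets alpha at 0.05 without saying one- or two-sided. The section on non-adherence and missing data {20c} says that people who no longer wish to take part are left out of the analysis.

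**The concern.** There are two separate matters.

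First, the allowance for attrition. An enrolment target that allows for a loss fraction has to be divided by the fraction retained, not multiplied by one plus the loss. With 26 required and 15% lost, the two methods give different whole numbers. Because {20c} removes withdrawn participants from the analysis, the number who remain is what carries the power.

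Second, the step from 0.42 (SD 0.13) to 26. A standardised effect size does not normally carry an SD of its own, so the printed pair can be read in several ways, and these lead to very different sample sizes. The 80% is the only power figure in the article. A reader who wants to know what size of effect the trial can detect, on which outcome, cannot work it out from what is printed.

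**Working it through.** **Attrition.** Inputs from Sample size {14}: 26 required, 30 enrolled, 15% lost.

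- Reproducing the plan's figure: 26 × 1.15 = 29.9, rounded up to 30. This is probably how 30 arose.
- Correct inflation: 26 / (1 − 0.15) = 30.6, so 31.
- Forward check: 30 × 0.85 = 25.5, below 26.
- Loss that 30 can bear and still leave 26: (30 − 26)/30 = 4/30 = 13.3%.

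Cost in power: for a two-sided paired t-test at 5%, 26 participants give 80% power for a standardised paired difference of 0.5717. The same difference with 25 participants gives 78.3%. The loss is 80.0 − 78.3 = 1.7 percentage points.

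**Where 26 comes from.** Inputs: 0.42, 0.13, 80% power, alpha 0.05. For a paired comparison with standardised difference dz and n participants, power is the probability that a noncentral t variable with n − 1 degrees of freedom and noncentrality dz × √n exceeds the critical t in absolute value.

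| Reading of 0.42 (SD 0.13) | n for 80% | Power at 26 |
|---|---|---|
| dz = 0.42, two-sided | 47 | 54% |
| dz = 0.42, one-sided | 37 | 67% |
| Raw mean 0.42 over SD 0.13: 0.42/0.13 = 3.23, two-sided | 4 | about 100% |
| 0.13 as uncertainty in dz, lower end 0.42 − 0.13 = 0.29 | 96 | 30% |
| 0.13 as uncertainty in dz, upper end 0.42 + 0.13 = 0.55 | 28 | 77% |

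None of these gives 26.

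**With a correlation supplied.** If 0.42 is the difference between two conditions in between-person SD units, then dz = 0.42 / √(2(1 − ρ)), where ρ is the within-person correlation. The article gives no ρ, so a range is assumed (two-sided, 5%):

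| ρ | n for 80% | Power at 26 |
|---|---|---|
| 0 | 91 | 31% |
| 0.5 | 47 | 54% |
| 0.7 | 29 | 76% |
| 0.75 | 25 | 83% |
| 0.8 | 20 | 90% |

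Setting dz = 0.5717 and solving: ρ = 1 − (0.42/0.5717)²/2 = 0.73. So 26 can be reached, at a correlation near 0.73.

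The contrast matters as well. If the test compares before-to-after change between two interventions, and all measurements are equally correlated, the variance term is 4(1 − ρ) in place of 2(1 − ρ). The correlation needed is then 1 − (0.42/0.5717)²/4 = 0.865.

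If 0.42 is Cohen's f, a repeated-measures F-test with two uncorrelated measures needs 25 (82.9% power at 26). With four measures it needs between 17 (ρ = 0) and 7 (ρ = 0.7).

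**The case against.** The strongest reply is that a paired t-test is not the planned analysis. The article says that the calculation was done in repeated-measures software, from pilot data, for a model with four interventions and two time points. Such a calculation needs a covariance structure, which a journal article may fairly leave to the full protocol. A within-person correlation near 0.73 is not implausible for repeated measurements on one person, and reading 0.42 as Cohen's f with two uncorrelated measures also lands close to 26. This stands: failing to reproduce a repeated-measures result with a simpler test and no covariance inputs does not show the result to be wrong. What it does not answer is that the article prints an effect size with an SD attached and defines neither, so the printed figures do not determine n.

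On attrition, the reply is that the gap is trivial. Four losses out of 30 still leave 26, the section on adherence {11c} reports no loss to follow-up so far, and {20c} covers only people who say they wish to stop, not every kind of loss. All of that limits the size of the point. It does not make 30 the right inflation of 26 for 15%.

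A reader might infer from the first row of the table that the trial has only 54% power, and that a null result would therefore mislead. The document does not support this. The 54% holds only if 0.42 is a standardised paired difference tested two-sided, and the article does not say so. The article also calls the trial exploratory {8} and proof-of-concept {31a}, and nowhere says that a null result would be taken as evidence of no effect.

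**Conclusion.** The attrition statement is wrong as written, by one participant: 31 are needed to expect at least 26 after 15% loss, and 30 leaves 25.5. With 25 completers, power is about 78%, provided that 26 does give 80% and that the paired-t approximation is close enough for a one-participant change.

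The 26 is not reproducible from the effect size as printed. Direct readings give 4, 37 or 47. A figure of 26 requires either a correlation near 0.73, with 0.42 in between-person SD units, or another reading that the article does not state. It is not shown to be false, and neither 54% nor any other single value should be put forward as the trial's power. Severity is minor: one small arithmetic slip and one definition that needs completing.

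**What to change.** In Sample size {14}:

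1. Restate the allowance. Either say that 30 enrolled tolerates about 13% attrition (4 of 30) with 26 remaining, or say that 15% attrition leaves 25 to 26 completers, with power of about 78% at 25 if 26 gives 80%.
2. Go back to the inputs used in the power software. State the outcome and contrast that 0.42 refers to, whether it is standardised or raw, what the 0.13 measures, whether the test is one- or two-sided, and the within-person correlation used.
3. If those inputs give a power other than 80% at 26, print that figure instead.

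The cost is a few reworded sentences and a look at the saved calculation. No extra participants are needed, though the stated power may come out lower.

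No change to the contrasts is called for. Pooling the four arms as an anodal-by-cathodal factorial to gain power would change what Aims one and two estimate. It would also assume additivity where Aim three sets out "to evaluate the confluent effect of bilateral THD-tDCS". An interaction of 0.42 on the same scale as a pairwise difference of dz = 0.42 has 0.42/√2 = 0.30 as its standardised size (equal correlations), and so only about 31% power at 26.

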### Recruitment {15}

The primary source of recruitment for this study is the Carle Foundation Hospital. The Carle clinical research team recruit participants who meet inclusion and exclusion criteria based on their medical history. Study personnel then establish an initial visit for these referrals. Other means of referral include word of mouth or Carle Health referrals.

## Assignment of interventions: allocation

### Sequence generation {16a}

The randomization order is also generated by a random sequence generator provided by REDCap (Research Electronic Data Capture) [26, 27].

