## Trial design {8}

This trial, conducted at the Carle Foundation Hospital, is an exploratory sham-controlled, double-blind, cross-over study designed to evaluate the effect of THD-tDCS on upper motor function in participants in the post-acute phase of stroke recovery. The study has four intervention arms: anodal stimulation (Fig. 1c), cathodal stimulation (Fig. 1d), bilateral stimulation (both cathodal and anodal) (Fig. 1e), and sham/placebo (Fig. 1f). Participants receive each intervention in a randomized order, with a 2-week washout period between each intervention.

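### The four-visit crossover model lists no visit term and the article names no balancing of treatment orders; visit and visit-by-time-point should be added to the model

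*Protocol article*

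**What the plan says.** Under Trial design {8}: "Participants receive each intervention in a randomized order, with a 2-week washout period between each intervention". Participant timeline {13} gives one intervention per visit, "for a total of four visits".

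Under Sequence generation {16a}: "The randomization order is also generated by a random sequence generator provided by REDCap". Implementation {16c} repeats this. Neither section mentions blocks, a Latin or Williams square, or a list of permitted orders. Neither says that the draw is unrestricted.

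Under Statistical methods {20a}: "Intervention type (anodal, cathodal, bilateral, and sham) and the time point (before or after stimulation) are defined as fixed factors". Participants are the random factor, and a separate examination of carry-over is planned. Visit is not in the list.

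Three other statements bear on the point. Concomitant care {11d} and section {18a} put the pre and post assessments at the same visit on the same day. Section {20c} excludes participants who withdraw. Sample size {14} aims for 30 enrolled, and on evaluable numbers it says "we determined the sample size of 26 will give 80% power at the 5% significance level for the targeted effect size".

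**The concern.** In a crossover over four visits, an intervention contrast is protected against visit effects in two ways: orders can be balanced so that each intervention falls equally often on each visit, or visit can be in the model. The article describes neither. This is more than a detail left for later, because the factor list is given and visit is not on it.

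The effect at risk is narrow. It is a visit trend in the within-visit change, for example a practice gain on the Fugl-Meyer that shrinks from the first session to the fourth. Where interventions are unevenly spread over visits, part of such a trend is read as a difference between interventions. Where they are evenly spread but visit is not modelled, the trend stays in the residual and widens the standard errors.

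**Working it through.** **Inputs.** Four interventions, four visits and 24 possible orders; 30 enrolled and 26 evaluable (Sample size {14}). The article gives no visit trend, so one is assumed below and shown over a range.

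**1. The plan's figure of 30.** 26 × 1.15 = 29.9, which rounds to 30. Dividing instead, 26 / 0.85 = 30.6, or 31. The stated 30 is close enough to use.

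**2. Spread over visits if each order is an independent draw from the 24 (assumption).** Each intervention-by-visit count has mean 30 / 4 = 7.5 and SD √(30 × 0.25 × 0.75) = 2.37. In 4,000 simulated trials the smallest of the 16 counts had median 4 and the largest had median 12 (5th to 95th percentiles 2 to 5 and 10 to 14). All 16 counts were 7 or 8 in about 0.03% of trials. Counts of which intervention immediately precedes which had median extremes of 4 and 11.

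**3. Gap in mean visit position between two interventions.** For one participant, a position has variance (4² − 1) / 12 = 1.25 and two positions have covariance −1.25 / 3 = −0.417. The difference has variance 2 × (1.25 + 0.417) = 3.33.

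- n = 30: SD of the mean gap = √(3.33 / 30) = 0.33 visits.
- n = 26: √(3.33 / 26) = 0.36 visits.
- Largest of the three gaps from sham at n = 30, simulated: 0.40 at the median and 0.77 at the 95th percentile.

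**4. What this does to a contrast.** Let the pre-to-post change drift by δ per visit (assumption; linear). A contrast is then off by δ × gap. On the Fugl-Meyer, where the article takes 5 points as the smallest clinically meaningful difference:

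| Assumed δ (points per visit) | Largest error, median | Largest error, 95th percentile |
|---|---|---|
| 0.25 | 0.10 | 0.19 |
| 0.5 | 0.20 | 0.39 |
| 1.0 | 0.40 | 0.77 |

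Over repeated randomisations the error averages zero. With σ² the within-participant variance of the change, the contrast variance rises from 2σ²/n to 2(σ² + 1.67δ²)/n, since 3.33 / 2 = 1.67.

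**5. What modelling visit costs.** With visit in the model and unrestricted orders, the contrast variance is on average 1.036 times 2σ²/n. The term therefore pays for itself once 1.67δ² exceeds 0.036σ², that is δ above √(0.036 / 1.67) = 0.15σ. In degrees of freedom, 26 completers give 26 × 4 = 104 changes. The residual is 104 − 26 − 3 = 75 without visit and 72 with it.

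**6. What balanced orders would add.** Four Williams sequences in blocks of 4, N = 30, against unrestricted orders, as multiples of 2σ²/n:

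| Quantity | Unrestricted | Williams | Saving |
|---|---|---|---|
| Intervention contrast, visit modelled | 1.036 | 1.001 | 3% |
| Intervention contrast, visit and carry-over modelled | 1.188 | 1.103 | 7% |
| Carry-over contrast | 1.753 | 1.606 | 8% |

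Under the Williams scheme all visit and predecessor counts are 7 or 8, and the largest gap from sham is about 0.13 visits at the 95th percentile. If 4 of 30 drop out at random, the median extreme counts become 5 and 7, and the first two factors become 1.007 and 1.117.

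**The case against.** The strongest reply is that unrestricted allocation is an inference. The article says only that REDCap generates the order, and the underlying table may already be restricted. The full protocol or analysis plan, neither of which is shown, may say so. This stands: every imbalance figure above is conditional on unrestricted draws. For comparison, a table using each of the 24 orders once before repeating any would give median extreme counts of 6 and 9 and a variance factor of 1.005 with visit modelled.

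Second, same-day pre and post measurement removes much of what a visit effect usually means. Recovery between sessions, familiarity with the procedures and accumulated practice mostly move both scores together and cancel in the change. This stands too, and it confines the concern to a trend in the change itself, for which the documents give no evidence either way.

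Third, the trial is exploratory and the precision at stake is small. That limits the weight of the point. It does not argue against a model term that costs almost nothing.

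Three stronger readings are tempting and are not supported:

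- A reader might infer that the intervention comparisons are biased. Orders are randomised, so the imbalance is chance error and not systematic.
- A reader might infer that carry-over cannot be separated from treatment. The carry-over contrast has variance 1.753 against 1.606, so it is estimable under either scheme with modest loss.
- A reader might infer that a Williams square would remove the problem free of charge. Thirty is not a multiple of 4, excluded withdrawals disturb the balance again, and blocks carry some predictability.

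**Conclusion.** The point holds as a low-cost improvement to the analysis model. The listed fixed factors leave visit out of a four-visit crossover, and no balancing of orders is described that would make the omission harmless to the contrasts. If orders are unrestricted, uneven spread is close to certain (counts of about 4 to 12 against 7.5), and a trend of δ per visit in the pre-to-post change would typically shift the worst-placed contrast with sham by 0.40δ. For assumed trends of 0.25 to 1 Fugl-Meyer point per visit, that is 0.10 to 0.40 points at the median and at most 0.77 at the 95th percentile, well below the article's 5-point threshold.

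The conclusion rests on two assumptions that the documents do not settle: that orders are unrestricted, and that some trend in the within-visit change exists. Without the first, most of the imbalance goes and only the wider residual remains. Without the second, nothing is lost by the present model.

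**What to change.** **Main change, for all participants.** Add visit and visit-by-time-point as fixed factors. Equivalently, analyse the within-visit change with intervention and visit as factors. A visit main effect alone in the stacked pre/post model is not enough, because it adjusts the level at each visit and not the pre-to-post change. The cost is 3 parameters in the change analysis or 6 in the stacked model and, if orders are unrestricted and there is no trend, about 3.6% of variance. If the full analysis plan already has these terms, only the article's factor list needs to be brought into line.

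**State the restriction.** Say whether the REDCap orders are drawn freely or from a balanced table.

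**Optional, only if orders are unrestricted.** For participants not yet randomised, load the four Williams-square sequences in mixed blocks of 4 and 8. This nearly balances visits and predecessors. The check used blocks of 4, and a partly filled block of 8 could leave slightly more imbalance. The 3% and 7% savings assume that all 30 participants follow the scheme. Recruitment began in October 2022, so the achievable gain is smaller. The costs are a new allocation table, a change of allocation method during the trial, and a small risk that late orders in a block can be guessed unless the list is concealed from those enrolling and assessing.

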### Concealment mechanism {16b}

The blinded team members will leave the room when the intervention is performed. The participants are also blinded to the intervention. The interventions for sham, anodal, cathodal, and bilateral stimulation require the same process and length of time and are indistinguishable from the participant’s perspective.

### Implementation {16c}

The randomization order is also generated by a random sequence generator provided by REDCap (Research Electronic Data Capture) [26, 27]. If participants express interest in participating in the study, a sub-investigator will contact them by phone and schedule an appointment. On this visit, research staff will explain the study to them and go through the consent process. After consent is obtained from the participant, the assessments and interventions are performed by trained research staff. The allocation sequence is generated by a member of the team who is not involved in subjective outcome measures including the Fugl-Meyer and MAS.

